## 5.2 Secondary Objectives and Endpoints

The following table 1 contains the secondary objectives and endpoint of the study

| Objective                                                                                                                                                  | Endpoint                                                                                                           |
|------------------------------------------------------------------------------------------------------------------------------------------------------------|--------------------------------------------------------------------------------------------------------------------|
| 1) To assess the reduction in ICU admission in patients treated with IFN versus control group within 28 days of randomization                              | ICU-free days at 28 days (Day 1 through Day 28)                                                                    |
| 2) To assess the reduction in number of deaths in IFN compared to control group (day 28)                                                                   | All-cause mortality (Day 1 through Day 28)                                                                         |
| 3) To evaluate the increase in proportion of participants returning to negative SARS-CoV 2 RT-PCR in IFN-treated versus control group at Day 14 and Day 28 | Negative SARS-CoV 2 RT-PCR at day 14 post-randomization
Negative SARS-CoV 2 RT-PCR at day 28 post-randomization |

|                                                                                                                    |                                                                                      |
|--------------------------------------------------------------------------------------------------------------------|--------------------------------------------------------------------------------------|
| 4) To assess the increase in SARS-CoV 2-Specific Binding Antibody Titers in IFN compared to control group (day 28) | Change from Baseline in SARS-CoV 2-Specific Binding Antibody Titers at day 14 and 28 |
| 5) To assess the safety of IFN-treated patients versus control group                                               | Incidence of adverse events                                                          |

For secondary endpoints, more detailed descriptions follow:

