- 1) ICU-free days at 28 days will be calculated as the number of days a patient is not in an ICU. Time Frame will be: Admission (day 0) to 28 days after admission (day 28). In case of death, it will be counted as 0 day;
- 2) All-cause mortality will be: total number of death events occurring within day 0 and day 28;
- 3) Negative SARS-CoV 2 RT-PCR is defined as an undetectable presence of SARS-CoV 2 genes, as determined by PCR on an adequate sampling of upper respiratory tract.
- 4) Change from Baseline in SARS-CoV 2-Specific Binding Antibody Titers is defined as the difference in anti-SARS-CoV 2-specific antibody levels measured at day 28 versus day 0;
- 5) Details on safety event are described in paragraph 9.4

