## 10. Statistical Plan

The primary analysis will be carried out on the primary endpoint on the intention-to-treat (ITT) population defined as all patients randomized receiving at least one dose of treatment.

The percentage of patients undergoing disease progression defined on rate of progression of NEWS2 score lasting more than 5 days will be calculated in two arms (IFN- $\beta$ 1a + standard of care vs standard of care) of the trial. For persons who died, a conservative approach will be adopted and death will be considered an event. The effect of treatment will be estimated through a logistic regression model including a dummy variable for treatment. The effect of treatment will be estimated through multivariable logistic regression model by accounting for the following

[figure not shown]

covariates: age, gender, co-morbidities. Moreover, NEWS2 score at baseline and setting of recruitment will be also considered.

All primary and secondary analyses will be carried out both on ITT population and on per-protocol population. Per-protocol population includes all subjects who were included in the ITT population that received the treatment as defined in the protocol and who completed the study with no major protocol violations.

Kaplan-Meier survival analysis and Cox proportional hazards model will be used for time-to-event data. The following covariates will be included in the Cox model: age, gender, co-morbidities. Moreover, NEWS2 score at baseline and setting of recruitment will be also considered. For the secondary endpoint ICU-free days, a competing risk model will be adopted considering death a competing event, following the method proposed by Fine and Gray (57). Moreover, the median difference will be reported.

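### ICU-free days is a day count with death scored 0, but section 10 gives it a Fine-Gray model with no defined event and a median difference that is very probably 0

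*Protocol*

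**What the plan says.** Table 1 in Protocol section 5.2 gives the first secondary objective as "To assess the reduction in ICU admission in patients treated with IFN versus control group within 28 days of randomization" and its endpoint as "ICU-free days at 28 days (Day 1 through Day 28").

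The detailed definition below the table reads "ICU-free days at 28 days will be calculated as the number of days a patient is not in an ICU". It gives the window as "Admission (day 0) to 28 days after admission (day 28") and adds "In case of death, it will be counted as 0 day".

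Section 10 prescribes the analysis: "For the secondary endpoint ICU-free days, a competing risk model will be adopted considering death a competing event", citing the Fine and Gray method, followed by "Moreover, the median difference will be reported". It names no event, no event time, and no rank or other test of the day count.

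Section 8.5 says that ICU admission, days in ICU and survival will be recorded for progressing patients.

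**The concern.** The endpoint and the model are different kinds of object. ICU-free days is one bounded number per patient, known in full at day 28, in which death has already been given the worst value. A Fine-Gray model describes the time to a defined event when another event can prevent it. Attaching the model to the count leaves the analyst to invent the event, and the choice changes what is estimated.

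The obvious choice, first ICU admission, is a sensible outcome, but it is not ICU-free days. A patient with one ICU day and a patient with twenty count the same. A patient who dies without entering an ICU scores worst in the count, whereas in the model that patient remains in the risk set as someone who never has the ICU event.

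The median difference would then be the only result on the endpoint's own scale. It can move only if about half of an arm has an ICU day or dies. At stake is a secondary result that does not estimate an effect on ICU-free days, or that shows 28 versus 28 when the arms differ.

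**Working it through.** The protocol states no figure for this endpoint, so there is none to reproduce. Arm sizes are from section 5.4: 40 IFN and 20 control.

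**1. What the model needs and what the endpoint gives**

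| | Endpoint (5.2) | Model (10) |
|---|---|---|
| Data per patient | one number of days | an event type and an event time |
| Death | value 0, the worst | competing event |
| Length of ICU stay | counts in full | ignored if the event is first admission |
| Event named | not applicable | none |

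**2. How often the median difference is exactly 0**

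Let q be the share of an arm with any ICU day or death by day 28; everyone else scores 28. For even n, the sample median is the mean of the (n/2)th and (n/2 + 1)th ordered values. It equals 28 when at most n/2 − 1 patients score below 28: at most 9 of 20 controls and at most 19 of 40 IFN patients.

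P(both medians = 28) = P(Bin(20, q_control) ≤ 9) × P(Bin(40, q_IFN) ≤ 19)

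The values of q are assumptions. For orientation only, section 1.1 says about 20% of infected people develop severe disease, and section 5.4 assumes progression in 50% of controls and 15% of IFN patients.

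| q control / q IFN | Control median 28 | IFN median 28 | Both 28 |
|---|---|---|---|
| 10% / 5% | >0.999 | >0.999 | >0.999 |
| 20% / 10% | 0.997 | >0.999 | 0.997 |
| 30% / 15% | 0.952 | >0.999 | 0.952 |
| 40% / 15% | 0.755 | >0.999 | 0.755 |
| 50% / 15% | 0.412 | >0.999 | 0.412 |

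The last row would require every progression assumed in section 5.4 to end in ICU or death.

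**3. What the two summaries miss**

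Simulated ICU-free days, with assumed admission on days 3 to 14, exponentially distributed stays cut off at day 28, and death = 0:

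- Admission 20% in both arms, no deaths, mean stay 14 v 7 days: mean ICU-free days 25.8 v 26.6. Admission incidence is equal by construction, and both medians are 28.
- Admission 20% and mean stay 10 days in both arms, deaths 15% v 5%: means 22.3 v 24.9, both medians 28.
- Admission 30% v 10%, mean stay 10 days, deaths 5% in each arm: means 24.0 v 25.7, both medians 28. With 20 and 40 patients the sample median difference is 0 in 90% of trials. A Mann-Whitney test on the same data has about 37% power: low, but it does use the information.

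**4. Time origin**

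Table 1 counts Day 1 to Day 28, and its objective counts from randomisation. The definition counts from admission, called day 0, to day 28. Day 1 to 28 is 28 days; day 0 to 28 inclusive is 28 − 0 + 1 = 29 days. Section 7.3 also enrols patients at home and in care homes. If admission means hospital admission, those never admitted have no starting point.

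**The case against.** **The model does fit the objective.** Objective 1 concerns ICU admission within 28 days of randomisation. A Fine-Gray model of time to first ICU admission, with death competing, addresses exactly that, and section 8.5 collects the data. A reader might infer that neither planned analysis can answer the ICU objective; the documents do not support that. What stands is that the model is assigned by name to ICU-free days, with no event defined.

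**Detail may sit in the SAP.** Event and time definitions for a secondary model are often left there, and scoring death as 0 could serve the median while death as a competing event serves the model. This is fair, and the protocol nowhere says that the count itself is the time variable. But the protocol does fix a model type to a count, and an SAP that follows it inherits the mismatch.

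**The median is only a descriptive addition.** A reader might infer that its difference will be 0 whatever the drug does. That is too strong: at 50%/15% the chance that both medians are 28 is only 0.412. The supportable statement is that 0 is very probable at plausible event rates.

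**Admission (day 0) may simply mean study entry.** The same list in section 5.2 uses day 0 as the start for deaths and as the antibody baseline. A reader might infer that the window differs by recruitment setting, for example that a home patient hospitalised on day 10 would be followed to day 10 + 28 = 38, beyond the last scheduled day T28. That holds only if admission means hospital admission. Even then, section 8.5 takes ICU outcomes from regional surveillance, so later data might be obtainable. What stands is a conflict in wording over the origin.

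**Conclusion.** The concern holds in this form. Section 10 assigns a time-to-event model to an endpoint that section 5.2 defines as a day count with death scored 0. The model has no stated event, the two sections treat death differently, and a first-admission model leaves out length of stay. The median difference is exactly 0 with probability at least 0.95 when up to 30% of controls and 15% of IFN patients have an ICU day or die. It becomes informative only as the control share approaches one half. These rates are assumed, because the protocol gives none. The time origin is worded inconsistently within section 5.2.

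The endpoint-model mismatch and the conflict over the origin can be read directly from the text and need no assumption about rates. The consequence is limited to one secondary endpoint, with few events likely in 60 patients; the primary analysis and the sample size are not touched. It should be corrected before analysis.

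**What to change.** 1. In section 5.2, use one window for every patient, Day 1 to Day 28 from randomisation, and remove the reference to admission. Keep death by day 28 = 0.
2. In section 10, compare ICU-free days between arms with a rank test stratified by sex, the randomisation stratum in section 9.1 (van Elteren), or with a proportional-odds model. Report an effect size with a 95% CI (probability index or odds ratio, with the mean difference if wanted) in place of, or alongside, the median difference.
3. Attach Fine-Gray and cumulative incidence at day 28 to a separately defined outcome: time from randomisation to first ICU admission, with death as the competing event. This addresses objective 1 directly.

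The cost is wording in sections 5.2 and 10 and slightly more analysis. Section 8.5 already provides for recording ICU admission, ICU days and survival, so no new data items are needed.

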## 11. Timing

See APPENDIX 2: Timeline scheme and APPENDIX 3: GANTT

## 12. Feasibility

Our study plans to enroll either hospitalized and non-hospitalized newly diagnosed COVID-19 patients, as well as patients hosted in long-stay residential care homes. The possible scenario of the Italian pandemic occurring during the conduction of the study will likely affect the proportion of patients that will be enrolled in the different settings. In fact, for patients presenting with mild illness, the decision to undertake hospitalization vs home care should be carefully evaluated to take into account patient risk of rapid deterioration, but also the burden on the health care system.

On august 11th, the ISS, together with the Ministry of Health and the Coordination of Italian regions and autonomous provinces, issued a document called “Elementi di preparazione e risposta a COVID-19 nella stagione autunno-invernale”. The document, aimed at providing general elements and suggesting preparedness frameworks to strengthen the response and optimally cope with any increase in the number of new infections by SARS-CoV 2 in the autumn-winter 2020-2021 season, foresees four possible scenarios, characterized by increasing SARS-CoV 2 transmission rate and related risk of SSN collapse.

To ensure that patients’ enrolment is duly completed in any of the possible scenarios, the study will count on a network of collaborating institutions directly involved in the identification and management of COVID-19 patients in Rome. A campaign will be held to inform Family doctors (Medici di Medicina Generale) and long-stay residential care homes (LSRCHs), whose collaboration will ensure the precocious identification of eligible patients throughout the urban area of Rome. The Special Unit for regional continued care (USCAR) are currently involved in the prompt identification of COVID-19 clusters within Regione Lazio. In this study, a group of physicians belonging to USCAR will be specifically trained and will be responsible for the screening, enrolling and clinical monitoring of patients kept under home isolation or hosted in long-stay residential care homes (LSRCHs).

All experts involved in the project are highly motivated, have complementary expertise and a strong background in the fields of IFN biology and infectious diseases. The CNR group, including the Sponsor Coordinator ([name]) and Scientific Coordinator ([name]) of the study, has a long-lasting expertise on immunology, IFN biology and clinical studies with IFN-I. The

[figure not shown]

Istituto Nazionale per le Malattie Infettive “Lazzaro Spallanzani (clinical center) is one of the five clinical hubs for COVID-19 management in town and has a longstanding experience in multicentre clinical studies and the PI ([name]) is a well-recognized clinician deeply involved in the clinical management of COVID-19 patients. The ISS group includes scientists with a background on IFN-I biology in both basic research and clinical trials ([name], [name], [name], [name], [name]) and with long record expertise on antibody response measurement ([name], [name]). Moreover, the Clinical Epidemiology group of the ISS ([name], [name], [name], [name]) has a strong background on statistical analysis and was involved in the recent survey on COVID-19 infection in long-stay residential care homes (58) . To ensure the full feasibility and the high quality performance of the study the Sponsor finalized a contract with a CRO, highly specialised in clinical studies involving IFN- $\beta$ , which will support the Sponsor Coordinator and the Scientific Coordinator with regard to specific services and for the implementation and monitoring of the entire study.

## 13. Good clinical practices and ethics

### 13.1. Good clinical practice

The study will be conducted in accordance with ethical principles founded in the Declaration of Helsinki (1964) and subsequent amendments and updates (Fortaleza, Brazil, October 2013), in the International Conference on Harmonization (ICH) for Good Clinical Practice (GCP) and in the appropriate regulatory requirements. The drug used in this trial is already registered and its toxicity profile is very well known, since it is largely used for the treatment of Multiple Sclerosis.

### 13.2 Ethical aspects

The entire study protocol, including informative material for the patients and modules for the informed consent, will be evaluated by The Ethics Committee (EC) of the National Institute for Infectious Diseases “Lazzaro Spallanzani”, Rome, Italy, which is the National Ethics Committee for evaluation of clinical trials on human drugs in COVID-19 patients.

The study will not start before obtaining a favorable opinion from the EC, the Competent Authority Authorization and any other authorization required by local regulation. Every intention to modify

[figure not shown]

any element of the original protocol after the first approval will be promptly notified to the EC and will be applied only after its written authorization. Investigators will be responsible for submitting any amendments to the protocol to the EC. Any modifications to the protocol, which may impact on the conduct of the study, may affect patient safety, including changes of study objectives, study design, patient population, sample size, study procedures or significant administrative aspects will require a formal amendment to the protocol. Such amendments will be agreed and approved by the Ethics Committee of the National Institute for Infectious Diseases “Lazzaro Spallanzani”, Rome, Italy, and the health authorities prior to implementation, in accordance with local regulation. Administrative changes of the protocol are minor corrections and/or clarifications that have no effect on the way the study is to be conducted. These administrative changes will be documented in a memorandum.

#### 13.2.1 Written informed consent

The Investigators will ensure that the subject is given full and adequate oral and written information about the nature, purpose, possible risks and benefits of the study. Subjects will also be notified that they are free to discontinue from the study at any time. The subject’s signed and dated informed consent will be obtained prior to conduct any procedure specific for the study. The original signed Written Informed Consent Form will be stored, and a copy will be given to the patient.

#### 13.2.2 Subject data protection

In order to protect the subjects’ identity, the Investigator will assign a subject identification number to each enrolled subject to be used instead of subject name when reporting all study related data and adverse events.

The Written Informed Consent Form will explain that the study data will be stored at Spallanzani Hospital maintaining confidentiality in accordance with national data legislation. However, the personal information must be available to authorized personnel of Study Sponsor (clinical monitor and auditor), Ethics Committee and Regulatory Authorities. In addition, consent to allow direct access to original medical records to ensure data verification will be obtained from the subject before participation in the study.

Enrolment log must be kept strictly confidential to enable patient identification at the site.

[figure not shown]

### 13.2.3 Audits and inspections

The Principal Investigator and the SC will provide all the necessary information and material to the participating centers in order to standardize all the protocol-related procedures and to avoid unexpected variability. Printed and electronic informative material (complete original protocol, informed consent modules, informative modules for patients and relatives, recruitment checklist, graphic timeline of interventions and visits, order list for physicians and nurses) will be distributed to Spallanzani Hospital and USCAR. Source data/documents must be available to inspections by the designee or Health Authorities.

### 13.2.4 Monitoring

The monitoring activities will be performed by a Clinical Research Organization. Clinical Monitor will perform the monitoring activities according to "Note of Guidance on Good Clinical Practice" (ICH E6 (R2), EMA/CHMP/ICH/135/1995).

The clinical monitor will maintain contacts between Investigators and Study Sponsor; furthermore, during the study the clinical monitor will verify that informed consent was obtained from all subjects, that the data were adequately documented in medical records and that the Investigators were compliant with the protocol. The clinical monitor will inform the study Sponsor and the Investigators about all detected protocol deviations, all facilities and technical Staff detected problems. The Investigators will provide direct access to source data/documents for data verification.

### 13.2.5 Declaration of interest

The study participants declare no financial and/or other conflicts of interest related to the study.

### 13.2.6 Dissemination policy

The Circ. Min. Health N° 6 of 09/02/2002 obliges each researcher who gets any results of interest to public health, to publish the results within 12 months from the end of the study. All the patients will freely agree or disagree to participate in the study in the belief that the results will be useful to improve knowledge about their pathologies, for health benefit from themselves or other patients. To respect their will and in the maximum interest of honest clinical research, the investigators agree on the need to ensure the wide publication and diffusion of their results in a consistent and

[figure not shown]

responsible way under their responsibility. The Study Coordinator is the official data owner. The Study Coordinator has the right to present methods and results of the study at public symposia and conferences. The principal publications from the trial will be in the name of Investigators with full credit assigned to all collaborating investigators and institutions.

### 13.3 Insurance

The study will be conducted according to the law about the study insurance agreement (DM 14 luglio 2009); *ad hoc* insurance n. A1202150060-LB has been established with Lloyd's Insurance Company S.A

[figure not shown]

## 14. Budget

| Materiale/Utilità                                             | Costo unitario | Numero per paziente | N. pazienti | Quantità | Totale        |
|---------------------------------------------------------------|----------------|---------------------|-------------|----------|---------------|
| Costi coordinamento medico                                    | 75000          |                     |             |          | 75000         |
| Rebif/Rebismart                                               | 0              | 1                   | 60          | 60       | 0             |
| Servizi svolti da CRO                                         |                |                     |             |          | 60000         |
| Saturimetro                                                   | 25             | 1                   | 30          | 30       | 750           |
| Sfingomanometro                                               | 20             | 1                   | 30          | 30       | 600           |
| DPI completo FFP3                                             | 10             | 10                  | 30          | 300      | 3000          |
| Assistenza domiciliare                                        | 400            | 1                   | 30          | 30       | 12000         |
| Teleassistenza                                                | 10             | 28                  | 30          | 840      | 8400          |
| Analisi del sangue                                            | 40             | 7                   | 60          | 420      | 16800         |
| Test Sars-CoV2                                                | 85             | 3                   | 60          | 180      | 15300         |
| Test sierologico                                              | 60             | 3                   | 60          | 180      | 10800         |
| Markers infiammatori                                          | 100            | 2                   | 60          | 120      | 12000         |
| Ddimero                                                       | 6              | 2                   | 60          | 120      | 720           |
| Proteina C Reattiva                                           | 6              | 2                   | 60          | 120      | 720           |
| Systemic immune profiling                                     | 356            | 3                   | 60          | 180      | 64080         |
| RT-PCR per IFN signaling                                      | 280            | 2                   | 60          | 120      | 33600         |
| Costi processamento campioni biologici                        | 30             | 7                   | 60          | 420      | 12600         |
| Assicurazione                                                 |                |                     |             | 1        | 9500          |
| Costi etichettatura e gestione farmaco                        |                |                     |             | 1        | 5000          |
| Costi generali per struttura coordinatrice                    |                |                     |             |          | 47730         |
| Medical Writing and Statistical Data Analysis (all endpoints) |                |                     |             |          | 50000         |
| Totale                                                 |                |                     |             |          | 438600 |

The study is co-funded by Merck Healthcare KGaA with a support equal to 40% of total costs.

